**Statistical Analysis, Data Analysis and Interpretation**

*Sample Size*

In the Pilot Natural History Study conducted in the GCRC at the University of Utah, we found that SMA Type 2 patients did not significantly change over a six-month period when measured with the Modified Hammersmith Functional Motor Scale-SMA (MHFMA-SMA). The standard deviation for this longitudinal group was 3.19. The two treatment groups differ over the first six months, thus the primary outcome will be change in Modified Hammersmith Functional Motor Scale-SMA from the second baseline to six months. A clinically meaningful change is taken to be a 3-point change. A sample size of 25 patients completing both the baseline and six-month evaluations will provide 90% statistical power with an effect size of 0.941, Type I error of 0.05 (two-sided). Assuming 20% attrition, then 60 total patients will be required.

The patients that can stand or walk will be evaluated in a cohort 2 arm. The primary endpoint will be the SMA-3 scales. When the sample size is 25, a two-sided 95.0% confidence interval for a single mean will extend 39% of the standard deviation from the observed mean; the confidence interval is based on the large sample z statistic. In order to ensure that 25 patients complete the therapy then 30 patients will be accrued.

*Statistical Analyses*

The primary aim is to compare change over the first six months on the MHFMA-SMA for the VPA+C arm versus placebo. The assumption of normality of the change scores will be checked, if it holds then a t-test will be performed comparing the difference in average change scores. Gender and age may affect MHFMA-SMA scores; as such a linear regression analysis that includes gender and age will be included along with treatment. This will be a confirmatory analysis. Subjects that drop out prior to six months will be excluded from the primary analysis. If the subjects had a 3-month evaluation then an additional analysis will be performed using the last observation carried forward approach to determine the effect on the outcome of subjects with missing data.

Secondary endpoints include an evaluation of the change in MHFMA-SMA at 12 months. We will evaluate the change from second baseline to 12 months and compare both groups. This will be done using a t-test. Since all patients will cross over to VPA+C at six months, this evaluation will be exploratory to determine whether or not additional treatment time of 12 vs 6 months leads to additional functional benefit in the treatment cohort compared to the placebo cohort and compared to their baseline values. We will also look at the change in MHFMA-SMA from 6 to 12 months for both groups. In addition, generalized estimating equations will be used to incorporate all longitudinal measurements from the second baseline through 12 months to determine if there is a sustainable treatment effect. Additional secondary endpoints include: Pulmonary Function Testing in subjects over five years of age, quantitative SMN mRNA, Peds QL™, CMAP amplitude/area, and MUNE. These endpoints will be exploratory in nature. Some will be hypothesis generating, while others will be confirmatory for the MHFMA-SMA results.

*The analyses of the cohort arm will be as follows:*

The assumption of normality of the change scores will be checked, if it holds then a large-sample z-statistic confidence interval around the mean will be constructed. Change from baseline will be examined and reported with 95% confidence intervals. Gender and age may affect scores; as such a linear regression analysis that includes gender and age will be performed to determine their influence. Subjects that drop out prior to six months will be excluded from the primary analysis. If the subjects had a 3-month evaluation then an additional analysis will be performed using the last observation carried forward approach to determine the effect on the outcome of subjects with missing data.

Additional secondary endpoints include: Pulmonary Function Testing in subjects over five years of age, Quantitative assessment of SMN mRNA, Peds QL™, Maximum CMAP amplitude/area: ulnar nerve /hypothenar eminence, Ulnar MUNE, growth and vital sign parameters, dietary assessment. These endpoints will be examined at each time point with means and confidence intervals as well as an analysis over time. These exploratory analyses will aid in the design of follow-up studies in this cohort of patients.

*Randomization*

Randomization will be performed using a permuted block design balancing for institution. Each institution must submit a Study Agent Shipment Form as soon as the individual responsible for the study agent has been identified and the site has institutional IRB approval for the study. The Shipment Form must be submitted to the Central Pharmacy in order to receive drug shipment with adequate processing time before calling to register the first case. Patients can be registered only after pretreatment evaluation is completed and eligibility criteria are met. Patients are registered prior to the start of any protocol therapy by calling the Statistical Office at Children’s Hospital of Philadelphia [contact], Monday through Friday, 8:30 a.m. to 5:00 p.m. ET. This process will be performed following screening visit 1 and verification by the lead Investigator at each study site that the subject meets all inclusion/exclusion criteria. The patient will be randomized/registered and a case number will be assigned and confirmed by email. After each randomization/registration, the Statistical Office will provide the double-blinded treatment assignment to the Central Pharmacy, who will ship the assigned therapy by next day shipment (Priority Overnight) to the institution. NOTE: Sites must plan ahead due to the following shipping schedule: Study agent/placebo for patients randomized after 4 p.m. ET will be shipped the following business day. Study agent/placebo will be shipped to U.S. sites Monday to Thursday only. Study agent/placebo will be shipped to Canadian sites Monday to Wednesday only. For example, study agent/placebo for a patient randomized to a U.S. site on Thursday after 4 p.m. will be shipped on the following Monday (or Tuesday, if Monday is a holiday). Study agent/placebo will not be shipped on holidays or December 23rd through January 2nd. Each institution is responsible for notifying the Central Pharmacy if study agent/placebo does not arrive on the expected date.

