**Study procedures**

All study patients from both cohorts will complete two baseline screening visits approximately one month apart. Upon completion of these baseline visits, patients will be divided into treatment arms and be given study medication. Patients in cohort 1 (SMA “sitters”) will be randomized to participate in either the treatment arm (group 1) or the placebo arm (group 2). Patients and investigators will remain blinded for the first six months of the study. After six months, patients in the treatment arm (group 1) will continue on study medication for an additional 6 months. All children enrolled in the placebo arm (group 2) will be switched to study medication and continue on treatment for six months. Thus, half the children will receive treatment for a full 12 months, while the other half will receive treatment for the last 6 months of the study. Patients in cohort 2 (SMA “standers and walkers”) will receive treatment for the entire 12 month time period.

Safety Labs will be drawn 2 – 4 weeks after screening visit 2 to assess safety labs and valproic acid and carnitine levels. This can be done via their local laboratories and the results would be faxed to the central study site. Any dosing adjustments needed will be coordinated through the medical monitor to keep investigators blinded until completion of the study. Additional safety labs for cohort 1 will be drawn 2-4 weeks after Screen 2, 6.5-7 months and 9 months. Additional safety labs for Cohort 2 will be drawn 2-4 weeks after Screen 2. Safety labs do not require a visit to the study site, but may be coordinated through patient’s local pediatrician.

**Cohort 1**: SMA “sitters”: 2 – 8 yrs

|  | Screen 1 | Screen 2 | Safety Lab 1 | Visit 1 | Visit 2 | Safety  Lab 2 | Safety Lab 3 | Visit 3 |
| --- | --- | --- | --- | --- | --- | --- | --- | --- |
|  | T-1 mo | T=0 | .5-1 mos | 3 mos | 6 mos | 6.5-7 mos | 9 mos | 12 mos |
| GROUP 1:  30 subjects | Baseline | Baseline  Start Drugs | VPA+ C | VPA+ C | VPA+C | VPA+C | VPA+C | VPA+C |
| GROUP 2:  30 subjects | Baseline | Baseline | Placebo x2 | Placebo x2 | Placebo x2 | VPA+C | VPA+C | VPA+C |

**Cohort 2:** SMA “standers and walkers”, ages 3 – 17 yrs

|  | Screen 1 | Screen 2 | Safety Lab 1 | Visit 1 | Visit 2 | Safety Lab 2 | Safety Lab 3 | Visit 3 |
| --- | --- | --- | --- | --- | --- | --- | --- | --- |
|  | T-1 mo | T=0 | .5-1 mos | 3 mos | 6 mos | 6.5-7 mos | 9 mos | 12 mos |

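### Minor arithmetic error in the Cohort 1 sample size: 60 enrolled with 20% attrition leaves 48 completers, not the 50 behind the 90% power, and power is then about 89%

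*Protocol*

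**What the plan says.** The Sample Size paragraph of the protocol (under Statistical Analysis, Data Analysis and Interpretation) builds the Cohort 1 figure in four steps.

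- Variability, from the pilot natural history study: "The standard deviation for this longitudinal group was 3.19".
- Target: "A clinically meaningful change is taken to be a 3-point change".
- Power: "A sample size of 25 patients completing both the baseline and six-month evaluations will provide 90% statistical power", at an effect size of 0.941 and a two-sided type I error of 0.05.
- Enrolment: "Assuming 20% attrition, then 60 total patients will be required".

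The Cohort 1 table under Study procedures lists "GROUP 1: 30 subjects" and gives the same number for Group 2, so the 60 are split equally between VPA plus carnitine and placebo.

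The Statistical Analyses paragraph plans a t-test on six-month change scores. It leaves patients who drop out before six months out of the primary analysis. Last observation carried forward is only an additional analysis.

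**The concern.** The power claim is tied to patients who complete both evaluations, so the attrition allowance has to turn completers into enrolled patients. The enrolment figure looks as if it was reached by adding 20% to the completers needed. The step that matches a 20% loss is to divide by the 80% expected to remain. The two give different answers, and adding 20% always gives the smaller one.

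What is at stake is whether sample size, attrition and power are consistent with one another. Under the protocol's own attrition assumption, the primary analysis would have fewer completers than the number on which the 90% rests. A reader who tries to reproduce the calculation will not get from 20% attrition to 60 patients.

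**Working it through.** **Inputs, all from the protocol.** Standard deviation 3.19; difference 3 points; effect size 0.941; two-sided alpha 0.05; 25 completers; 20% attrition; 60 in total (Sample Size). Thirty per group (Study procedures, Cohort 1 table). Two-sample t-test on completers only (Statistical Analyses).

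**1. Effect size.** 3 / 3.19 = 0.940, which agrees with the stated 0.941 up to rounding.

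**2. Reproduce the stated power.** For n per arm, the two-sample t-test has 2n − 2 degrees of freedom and noncentrality d × √(n/2). With n = 25 and d = 0.941:

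- noncentrality = 0.941 × √12.5 = 3.327
- degrees of freedom = 48, critical value 2.011
- power = **90.3%**

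The stated 90% is reproduced with 25 per arm. Solving the same formula for exactly 90% gives n = 24.73, so 25 is the smallest whole number per arm that reaches the target.

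**3. Apply the stated attrition to the stated enrolment.** 60 × (1 − 0.20) = **48 completers**, or 24 per arm. That is two fewer than the 50 required.

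**4. Where the 60 comes from.** 50 × 1.2 = 60. The inflation that keeps 50 after a 20% loss is 50 / (1 − 0.20) = 62.5, so **63** patients, or **64** with equal arms (25 / 0.8 = 31.25, so 32 per arm). The stated figure is 3 to 4 patients short.

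**5. The attrition that 60 does cover.** 1 − 50/60 = **16.7%**.

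**6. Power at the stated attrition.** With n = 24, the noncentrality is 0.941 × √12 = 3.260 on 46 degrees of freedom, with critical value 2.013.

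| Completers | Power, t-test (d = 0.941) | Power, normal approximation (d = 3/3.19) |
| --- | --- | --- |
| 25 + 25 | 90.3% | 91.4% |
| 24 + 24 | 89.1% | 90.3% |
| 22 + 26 | 88.9% | not calculated |
| 20 + 28 | 88.2% | not calculated |

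If each patient independently has a 20% chance of dropping out, the t-test power averaged over the possible splits is 88.8%. In every case considered here, the t-test power stays within 2 points of 90%.

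**The case against.** The strongest reply is that nothing practical depends on this. By the normal approximation, 48 completers still give 90.3%, so on that method the target is met. By the t-test the loss is 1.2 points (90.3% to 89.1%). With 24 per arm, 90% power is reached for an effect of 0.956, which at a standard deviation of 3.19 is 3.05 points instead of 3.00. A standard deviation of 3.25, about 2% above the pilot value, would cost about as much with all 50 completers (power 89.2%). All of this stands, and it is why the point is minor. It does not make the sentence right: the protocol plans a t-test, and 60 patients at 20% attrition do not yield 50 completers under either method.

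Two stronger readings are tempting, and the document supports neither.

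- A reader might infer that the trial fails to deliver its power. A figure of about 89% against 90% does not bear that out.
- A reader might take the 25 as the total for both arms, because the sentence does not say per arm. The protocol rules this out: the next sentence marks 60 as the total, the table shows 30 in each group, and 25 completers out of 60 would imply attrition of 1 − 25/60 = 58%, against the stated 20%. Only 25 per arm reproduces the 90%. The missing label is a matter of wording, not of design.

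**Conclusion.** The stated combination of 60 patients, 20% attrition and 25 completers per arm is arithmetically wrong. Enrolment of 60 leaves 48 completers at 20% attrition, or 50 at 16.7%; keeping 50 at 20% needs 63 patients, or 64 with equal arms. Power under the planned t-test is about 89% instead of 90%. This is a small shortfall and a minor correction.

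The power figures take the protocol's effect size of 0.941 and two-sided alpha of 0.05 as given, and assume equal allocation and a completers-only primary analysis, as the protocol plans. They assume losses that are equal between the arms, except in the uneven splits and the averaged figure shown in the working.

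**What to change.** Leave enrolment as it is and restate the sentence, for example:

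> Twenty-five patients per arm (50 completers) give 90% power. Enrolling 60 allows for 16.7% attrition; at 20% attrition, 24 per arm remain and power is about 89%.

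Adding per arm also supplies the missing label. The cost is one corrected sentence and a slightly less favourable power figure at 20% attrition. Enrolment, conduct and analysis are unchanged. If the sponsor prefers to keep both 20% attrition and 90% power, the matching enrolment is 63, or 64 with equal arms, which costs 3 to 4 more patients for about one point of power.

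The Cohort 2 figure (25 completers, 30 accrued) needs no change on this ground, because no attrition rate is stated there for it to contradict.

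### Cohort 2's stated precision (39% of the SD, from 25 completers out of 30 accrued) is slightly too favourable: no attrition rate supports the accrual, and a z interval at this size covers about 93.8%, not 95%

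*Protocol*

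**What the plan says.** Under Sample Size (protocol, Statistical Analysis, Data Analysis and Interpretation), the size of Cohort 2 rests on one precision statement. At n = 25, "a two-sided 95.0% confidence interval for a single mean will extend 39% of the standard deviation from the observed mean", and "the confidence interval is based on the large sample z statistic". The accrual target follows: "In order to ensure that 25 patients complete the therapy then 30 patients will be accrued". No attrition rate is given for this cohort.

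The only attrition rate in the document is in the preceding paragraph, for Cohort 1: "Assuming 20% attrition, then 60 total patients will be required". That rate goes with a calculation at six months: "A sample size of 25 patients completing both the baseline and six-month evaluations will provide 90% statistical power with an effect size of 0.941".

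Two other places bear on what completion means. Study procedures says that Cohort 2 patients "will receive treatment for the entire 12 month time period". Statistical Analyses says, for Cohort 2 as for Cohort 1, "Subjects that drop out prior to six months will be excluded from the primary analysis". The Cohort 2 paragraph there also specifies a large-sample z interval for the mean change, and does not name the visit at which that change is taken.

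**The concern.** The precision figure is the sole justification for the size of Cohort 2, so it should describe what the cohort can be expected to deliver. Three things stand in the way.

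- The step from 25 to 30 has no stated attrition rate behind it. It is the same step as in Cohort 1 (25 to 30 per arm, 60 in total), where it is labelled 20%. That suggests multiplication by 1.2 where division by 0.8 was needed.
- The half-width uses a z multiplier although the SD will be estimated from about 25 patients, so the interval is too short for its nominal level.
- The sentence speaks of completing therapy, which lasts 12 months, while the exclusion rule for the primary analysis works at six months. The number of completers therefore has no defined time point.

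What is at stake is an honest statement of precision. Cohort 2 is a single-arm, exploratory cohort, and no power claim or decision threshold hangs on the figure.

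**Working it through.** **Inputs.** Target 25, accrual 30, half-width 39% of the SD by z (Sample Size, Cohort 2). Attrition 20% (Sample Size, Cohort 1). Treatment for 12 months (Study procedures). Exclusion of dropouts before six months (Statistical Analyses, Cohort 2).

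**1. The stated precision.** Half-width / SD = 1.96 / √n. At n = 25 this is 1.96 / 5 = 0.392, so the 39% is reproduced.

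**2. The loss that 30 covers.** 1 − 25/30 = 16.7%. At that rate, 25 / (1 − 1/6) = 30 exactly.

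**3. The 20% rate, if borrowed from Cohort 1.**
- Expected completers: 30 × 0.80 = 24.
- Accrual needed for 25: 25 / 0.80 = 31.25, so 32.
- The figure 30 is what 25 × 1.2 gives.
- Half-width by z at n = 24: 1.96 / √24 = 0.400. Attrition alone moves the figure from 39% to 40% of the SD.

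**4. Is 25 ensured?** With independent dropout, the binomial probability that at least 25 of 30 complete is:
- 62% at 16.7% loss;
- 43% at 20% loss.

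**5. Coverage of the z interval.** With an estimated SD and normal change scores, the coverage at n = 25 is P(|t| < 1.96) on 24 degrees of freedom, which is 93.8%. Using t instead:
- n = 25: 2.064 / √25 = 0.413;
- n = 24: 2.069 / √24 = 0.422.

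**6. Month 12, on an added assumption.** The document gives no attrition for months 6 to 12.

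| Assumption | Completers at month 12 | z half-width / SD | t half-width / SD |
|---|---|---|---|
| 20% is the total loss over 12 months | 30 × 0.80 = 24 | 0.400 | 0.422 |
| A further 20% is lost in months 6 to 12 | 30 × 0.80 × 0.80 = 19.2, about 19 | 1.96 / √19 = 0.450 | 2.101 / √19 = 0.482 |

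Under these two readings the number of 12-month completers ranges from 19 to 24. In both, 24 patients reach month 6.

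**The case against.** The strongest reply is that nothing here is an arithmetic error. The move from 25 to 30 is exact at 16.7% loss, and no conflicting rate is stated for Cohort 2. The z basis is disclosed and matches the planned analysis, so 39% correctly describes the interval that the protocol intends to compute. Borrowing 20% costs one patient and about one percentage point of the SD. Cohort 2 is exploratory, so no conclusion turns on this.

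Most of that stands, and it is why the point is minor. It does not rescue the wording. If 16.7% was intended, it is not stated, and even at that rate the target is missed 38% of the time. Disclosing z does not make the interval a 95% interval when the SD is estimated from 25 patients.

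A reader might infer something stronger: that on the plan's own attrition only about 19 patients complete the 12-month therapy, and that the interval is 23% wider than stated (0.48 against 0.39). The document does not support this. The 20% belongs to Cohort 1 and is never described as a rate per six months, so applying it twice is an added assumption. The 23% also mixes two effects, fewer patients and a change from z to t; by z alone, n = 19 gives 0.450, about 15% wider. And the exclusion rule operates at month 6, so 24 patients would remain for a six-month analysis even then.

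**Conclusion.** The concern holds in a limited form. The stated precision is slightly too favourable: about 42% of the SD is realistic (t, n = 24) against the stated 39%. Most of that gap comes from z to t at the same n (0.392 to 0.413), and the rest from one patient fewer (0.413 to 0.422). The claim that 30 accrued will ensure 25 completers is unsupported at either rate considered.

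This rests on three assumptions: that Cohort 1's 20% applies to Cohort 2, that dropouts are independent (for the 62% and 43%), and that change scores are normal (for the 93.8%). The figure of 19 completers at month 12 is one end of a range that depends on an unstated second loss, and is not a finding about the plan. What the document does leave unresolved is whether completion is judged at month 6 or month 12. Severity is minor.

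**What to change.** Keep 30 patients and make these changes.

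1. In Sample Size, remove the word *ensure* and restate the sentence, for example: *Assuming 20% attrition, about 24 of 30 patients are expected to complete, and the 95% t interval for a mean will extend about 42% of the SD.* If a different rate is intended for Cohort 2, state it with the period it covers and recompute.
2. Replace the z interval by a t interval both in Sample Size and in the Cohort 2 paragraph of Statistical Analyses. Changing only one would create a contradiction.
3. Say whether completing the therapy means month 6, as in the exclusion rule, or month 12, as in the treatment period. If month 12, give the attrition assumed up to then. Should a further 20% loss after month 6 be assumed, label it as an assumption and quote about 19 completers and a t half-width of 48% of the SD.

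The cost is a few sentences in two sections and a slightly less favourable precision figure. No patients are added.

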The GCRC Informatics Core will serve as the infrastructure for a data coordinating center (DCC). The GCRC Informatics Core will be responsible for applying the best practices of data management, study design, safety reporting and clinical trial conduct to clinical research protocols. It will also provide project direction and management, data security and other necessary support from existing resources within the GCRC Informatics Core. There will be additional staff required for this project, a part time Database Administrator (DBA) and a full time clinical coordinator. Each study center will have complete access to its own patient population date that is centrally stored at Utah. Study populations and their resulting data are combined to create a large enough sample for clinical and statistical significance. Interim results, which are already deidentified, will be compiled by the GCRC informatics director and shared with co-investigators and collaborators as the data pertains to their own specialties.

Regular conference calls including *all* multi-center staff (PIs, coordinators, data manager, physical therapists, etc.) allow for discussion of problems, possible changes to protocol, plans for interim data collection, analysis, and publication. Each conference call is summarized in minutes and distributed to all multi-center staff.

**Participating Sites outside the University of Utah:** The other five sites involved in the multi-center study are located at the Children’s Hospital of Michigan at Wayne State University; Johns Hopkins Hospital and Johns Hopkins University; University of Wisconsin Medical School, Ohio State University, and Centre de Recherche de l'Hôpital Sainte-Justine in Montreal, Canada. Each of the site PIs are named co-investigators of this study. All participating sites maintain IRB approval and are equipped to handle safety concerns as they may arise. Safety of information is handled as described above: participants’ private health information is deidentifed before being sent to the central data site at Utah and then kept in locked cabinets. Participants’ health safety is protected in numerous ways: reactions to the study drug through regular lab draws, oversight of labs by the Central Lab coordinator, an unblinded study coordinator, and the Medical Monitor; reporting of Adverse Events as stipulated by the IRBs and medical follow-up as needed; and overnight care at the different university’s GCRCs or equivalent.

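### The Cohort 1 primary t-test on change could be replaced at almost no cost by one baseline- and site-adjusted model that uses both pre-treatment MHFMS scores

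*Protocol*

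**What the plan says.** The Sample Size paragraph defines the endpoint from one baseline: "thus the primary outcome will be change in Modified Hammersmith Functional Motor Scale-SMA from the second baseline to six months". Under Statistical Analyses the primary comparison is conditional on a check that the change scores are normal: "if it holds then a t-test will be performed comparing the difference in average change scores". The protocol names no alternative for the case where the check fails. It then adds a second model, in which "a linear regression analysis that includes gender and age will be included along with treatment. This will be a confirmatory analysis". Neither analysis contains baseline MHFMS as a covariate or a term for institution.

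The Randomization paragraph says "Randomization will be performed using a permuted block design balancing for institution". Administrative Responsibilities refers to "The other five sites involved in the multi-center study", which with Utah makes six institutions.

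Study procedures says "All study patients from both cohorts will complete two baseline screening visits approximately one month apart", and the procedure table marks functional testing at both Screen 1 and Screen 2. The secondary longitudinal model (generalized estimating equations) also starts at the second baseline, so the Screen 1 score is collected but used in no stated efficacy analysis.

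**The concern.** The trial is small: 30 children per arm, with 25 completers per arm assumed. A change score subtracts the baseline with a coefficient fixed at one, which is less efficient than estimating that coefficient. A single baseline carries the full visit-to-visit noise of one assessment, although a second assessment a month earlier is available for every child. When allocation is balanced within sites and the analysis ignores site, any between-site difference stays in the standard error although the design has removed it from the treatment contrast. Making the primary test depend on a preliminary check of the same data also leaves the primary analysis unsettled until the data are seen. At stake is precision, and a primary analysis that is fixed in advance.

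**Working it through.** **Inputs.** From Sample Size: difference 3 points; SD 3.19 ("The standard deviation for this longitudinal group was 3.19"), read here as the SD of six-month change, which the text does not state outright; effect size 0.941; two-sided 0.05; 25 completers, read as per arm. From the site list: six institutions. Assumed, because the documents give no figures: correlation ρ between a baseline and month 6 of 0.7 to 0.95; correlation ρ_b between the two baselines; site intraclass correlation (ICC) of 0 to 0.2.

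**1. The plan's own figure.** 3/3.19 = 0.940. The noncentral t with noncentrality 0.941 × √(25/2) and 48 degrees of freedom gives power 0.903, so 25 per arm and 90% reproduce. The design is sized for the unadjusted t-test.

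**2. Baseline adjustment.** Take equal variance σ² at each visit.
- Change from Screen 2: 2(1 − ρ)σ²
- Linear model adjusting for Screen 2: (1 − ρ²)σ², a ratio of (1 + ρ)/2 to the change score
- Linear model adjusting for the mean of both baselines: [1 − 2ρ²/(1 + ρ_b)]σ²; with ρ_b = ρ the ratio is (1 + 2ρ)/(2(1 + ρ))

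Power is at 25 per arm with SD 3.19 × √ratio and one degree of freedom charged.

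| ρ | Screen 2 only: ratio, power | Both baselines, ρ_b = ρ: ratio, power |
|---|---|---|
| 0.7 | 0.85, 0.942 | 0.706, 0.972 |
| 0.9 | 0.95, 0.916 | 0.737, 0.967 |
| 0.95 | 0.975, 0.910 | 0.744, 0.965 |

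So variance falls by 2.5 to 15% with the second baseline alone and by about 26 to 29% with both.

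Two visits a month apart may agree more closely with each other than with month 6, and the gain is then smaller. At ρ = 0.7, ρ_b = 0.85: (1 − 0.98/1.85)/0.6 = 0.784. At ρ = 0.9, ρ_b = 0.98: (1 − 1.62/1.98)/0.2 = 0.909. Over the combinations tried the cut is about 9 to 22%. That cut includes the part due to adjustment itself. At ρ = 0.7, ρ_b = 0.98 the ratio is 0.842, against 0.85 for Screen 2 alone, so there Screen 1 adds almost nothing.

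**3. Where ρ may lie.** The implied cross-sectional SD is 3.19/√(2(1 − ρ)): 4.12 at ρ = 0.7, 7.13 at 0.9 and 10.09 at 0.95. A uniform spread over the eligible MHFMS range of 2 to 37 has SD 35/√12 = 10.1. A wide spread of baseline scores would therefore put ρ near 0.90 to 0.95, where adjusting for the second baseline alone gains only 2.5 to 5%.

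**4. Institution.** Simulation with six sites, 50 completers, balanced allocation within site and 20,000 runs:

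| Site ICC | Type I error, t-test | Power, t-test | Power, site-adjusted |
|---|---|---|---|
| 0 | 0.050 | 0.904 | 0.903 |
| 0.05 | 0.047 | 0.909 | 0.916 |
| 0.1 | 0.041 | 0.916 | 0.928 |
| 0.2 | 0.035 | 0.928 | 0.952 |

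**5. Cost of the covariates.** One baseline term, age and five site indicators make seven terms. At 24 per arm (60 × 0.8 / 2) the unadjusted power is 0.891. In simulation, allowing for lost degrees of freedom and chance covariate imbalance, adjusted power is about 0.87 if the terms explain none of the variance of change, 0.89 at 5%, 0.90 to 0.91 at 10%, 0.93 at 20% and 0.95 at 25%. Break-even lies between about 5 and 10%.

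**The case against.** The planned test is valid and meets its stated power. Taking the last pre-treatment value as baseline is conventional, and the protocol says so openly. Seven covariate terms can lose power if they explain little. A fallback for non-normal data is the kind of detail a statistical analysis plan, not shown here, may hold. All of this stands. It makes the point an improvement rather than a correction, and the absence of a named fallback is not itself counted. What the protocol does fix is the gate, the unadjusted test and the single baseline.

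Four stronger readings are tempting, and the documents do not support them.
- *Two confirmatory analyses compete.* Only the regression is called confirmatory. The protocol later uses the word of secondary endpoints that corroborate the MHFMS result. Read that way, the regression supports the t-test, and one clarifying sentence is enough.
- *The plan ignores baseline and age.* A change score uses baseline by subtraction, and the regression adjusts for age. What is missing is adjustment for baseline, and age in the primary test.
- *A chance baseline imbalance feeds straight into the estimate.* With equal variances only a fraction (1 − ρ) passes through, so 5 to 10% at ρ of 0.95 to 0.90.
- *The result is biased or the trial underpowered.* Randomisation protects the estimate, omitting site errs on the conservative side, and power is 0.903 at the planned 25 completers per arm.

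**Conclusion.** The point holds as a cheap improvement to the Cohort 1 primary analysis. It is neither an error nor a source of bias. The loss is precision, of a size the protocol does not allow to be fixed. Using both baselines is the larger gain under equal correlations, and it shrinks as the two baselines agree more closely with each other than with month 6. Adjusting for the second baseline alone is probably worth only a few per cent of variance if baseline scores are widely spread. Adding institution aligns the analysis with the randomisation and matters only if sites differ. The ranges rest on 3.19 being the SD of change, on equal variances across visits and on the assumed correlations and site ICCs. Removing the normality gate is worthwhile whatever those values are, because it fixes the primary analysis before the data are seen.

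**What to change.** Name one primary analysis, used whatever the normality check shows: a linear model of month 6 MHFMS (or change) on treatment, pre-treatment MHFMS (mean of Screen 1 and Screen 2), age and institution. Pool small sites by a rule set before unblinding. Keep the t-test and a rank-based or re-randomisation test as sensitivity analyses, and state that the gender-and-age regression is supportive.

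Before Screen 2 is used as a covariate, reconcile two places on its timing: Study procedures assigns arms after both baseline visits, while the Randomization paragraph places randomisation after screening visit 1.

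The change is one of wording, since every variable is already collected. The price is about seven degrees of freedom, or one to two points of power if the covariates explain almost nothing.
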